### Secondary outcomes analysis

The effect of treatment on each of the psychological clinical measures will be analyzed using a longitudinal mixed-effects regression model similar to the methods described above to model the longitudinal trends in employment outcomes. The dependent variable will be the outcome score at baseline and each follow-up time point. Each follow-up visit will be categorized by the weeks since enrollment and an indicator for calendar month when the visit occurred will also be included in the model to control for seasonality. We will formally test for differences in outcomes at 18 months using predicted-marginal means. All hypothesis tests are pre-specified so there is no compelling reason to adjust the alpha level for multiple comparisons, and because they are likely to be correlated, a Bonferroni correction would be expected to be overly conservative. However, to aid interpretation we will use the Benjamini–Hochberg method to control the family-wise false-discovery rate for the secondary outcomes to be ≤ 10%.

Both between-treatment condition and within-treatment condition effect sizes for primary and secondary outcomes will be presented: Cohen’s *d* for continuous outcomes and the number needed to treat for dichotomous outcomes. An estimate of the 95% confidence interval will accompany each effect size in order to guide interpretation. Effect sizes indicate the magnitude of the treatment effect based on clinical significance and are independent of sample size and hence statistical significance.

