### Randomization and follow-up schedule

Participants who meet eligibility criteria are randomized (1:1) to either IPS or non-IPS-VR. Randomization uses a permuted block design of randomly varying block sizes stratified by site. Once assignment is made, the participant is analyzed in that group regardless of future events or services rendered, in accordance with the intent-to-treat principle.

Once informed consent is obtained, baseline assessments are administered. Participants are assessed at baseline and every 2 months (months 2, 4, 6, 8, 10, 12, 14, 16) and then final assessment at month 18 for employment outcomes and secondary outcomes. At each research visit, participants are assessed for the occurrence of adverse events or serious adverse events. The 18-month follow-up period allows for start-up time involved in each intervention prior to establishing competitive work and allows enough time for a participant to establish steady competitive work and achieve the secondary outcome goals.

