### Primary outcome analysis

The target sample size is 120 randomized participants (60 per study arm). The sample size was based on our most recent IPS study at the Tuscaloosa VA Medical Center that evaluated IPS in the primary care setting as nearly half of the participants had a SUD diagnosis. We expect that more than 84% will complete the intervention as randomized and greater than 95% will provide analyzable employment data. The between-group effect size was 0.55 in favor of IPS in the prior study, for which our projected sample size (54 per group with > 2 months data) would provide > 81% power. Very conservatively assuming that only 90% provide analyzable data this yields approximately 54 participants per group. This provides 80% power to detect a difference in means between groups of 0.54 standard deviations for a continuous outcome. The primary employment outcome is the number of weeks with competitive employment over the 18-month follow-up period. A week scored as “worked” is one in which a competitive job was held for any number of hours or days during that week. A week scored as “not worked” is one in which there was no competitive job held, or there were no employment data (i.e., early exit or missing data). The analysis of the primary outcome will use longitudinal mixed-effects regression models considering the cumulative number of weeks worked at each assessment as the dependent variable and study arm (IPS vs. non-IPS-VR) as the main independent variable adjusted for gender. Study site will be treated as a random effect, as will participant to account for the nesting of participants within sites and the multiple observations per person. We will initially specify the covariance structure of the repeated outcomes as unstructured and will proceed respectively to autoregressive and exchangeable structures if convergence issues are encountered. Prior to final modeling we will examine longitudinal plots of the employment data by group to evaluate whether the most appropriate model and any possible interaction effect appears to be additive (linear regression) or multiplicative (suggesting negative binomial regression), whether time should be included as categorical or linear, and whether it appears that a group*time interaction term is required to faithfully model the data.

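### The secondary models treat the baseline score as one of the outcomes without stating any baseline adjustment, so the month-18 test forgoes precision and may be diluted if the arm-by-time term is dropped

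*Protocol article*

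**What the plan says.** The Secondary outcomes analysis section of the protocol article covers the psychological measures with a "longitudinal mixed-effects regression model similar to the methods described above". It fixes the outcome vector: "The dependent variable will be the outcome score at baseline and each follow-up time point". It also fixes the test: "We will formally test for differences in outcomes at 18 months using predicted-marginal means". That is a difference in level at month 18, not in change from baseline.

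The methods it refers back to are in Primary outcome analysis. There the model has "study arm (IPS vs. non-IPS-VR) as the main independent variable adjusted for gender". The analysts will "initially specify the covariance structure of the repeated outcomes as unstructured", with simpler structures as fallbacks. Plots by group decide "whether it appears that a group*time interaction term is required to faithfully model the data".

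Other adjustments are mentioned: calendar month of the visit in the secondary models, and type of OUD medication in all models (MOUD outcome assessment). None of them is the baseline value of the score being analysed.

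**The concern.** Using baseline as one of the repeated outcomes is legitimate. What matters is whether the arm effect is switched off at that visit. Arm enters the primary model as an ordinary main effect and no constraint is stated, so the natural reading is that the arms are free to differ at baseline. There are then two cases.

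- **Arm-by-visit term fitted.** The free baseline difference absorbs the baseline information. The month-18 contrast is essentially the raw month-18 difference, with wider intervals than the data allow, and a chance baseline gap passes into it in proportion to the correlation.
- **Arm-by-time term left out.** There is one arm effect for all visits. The predicted difference at 18 months is that pooled effect, and it includes a visit at which no treatment effect can exist.

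The point applies to all the psychological scores analysed this way. The primary outcome, weeks worked since randomization, is not affected.

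**Working it through.** **Inputs from the protocol article.** Allocation is 1:1 ("are randomized (1:1) to either IPS or non-IPS-VR"). For visits, "Participants are assessed at baseline and every 2 months (months 2, 4, 6, 8, 10, 12, 14, 16", with a final one at month 18, so 1 + 8 + 1 = 10 visits. Primary outcome analysis gives 54 analyzable participants per group and 80% power at 0.54 SD. That figure belongs to the primary-outcome sample-size text; the article gives no power for the psychological scores, so it is borrowed as an illustration.

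**Assumptions.** Two-sided 5% level, SD of 1 at each visit, and a baseline to month-18 correlation ρ of 0.3 to 0.6. The article does not give ρ.

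**Step 1: the plan's own figure.** Standard error of a difference in means = √(2/54) = 0.192 SD. Detectable difference at 80% power = (1.960 + 0.842) × 0.192 = 0.539 SD by the normal approximation, or 0.544 SD with the t distribution. Power at 0.54 SD is 80.1% (normal) or 79.4% (t). The stated figure reproduces.

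**Step 2: arm by categorical visit, arms free at baseline.** With complete data and unstructured covariance, each arm-by-visit mean is estimated by its sample mean. The month-18 contrast is the raw difference, with standard error 0.192 SD whatever ρ is. A generalized least squares calculation over the 10 visits confirms this.

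**Step 3: common baseline mean, or baseline as a covariate.** The contrast becomes D18 − ρ·D0, where D0 and D18 are the arm differences at baseline and month 18. Its variance is (2/54)(1 − ρ²), so the detectable difference is 0.544 × √(1 − ρ²).

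| ρ (assumed) | Variance reduction | Standard error (SD) | Detectable difference (SD) | Unadjusted n per arm for the same precision, 54/(1 − ρ²) |
|---|---|---|---|---|
| 0.3 | 9% | 0.184 | 0.52 | 59 |
| 0.4 | 16% | 0.176 | 0.50 | 64 |
| 0.5 | 25% | 0.167 | 0.47 | 72 |
| 0.6 | 36% | 0.154 | 0.44 | 84 |

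**Step 4: chance baseline differences.** The baseline difference itself has standard error 0.192 SD, so a gap of 0.2 SD is about one standard error. Its expected carry-over is ρ × 0.2, or 0.10 SD at ρ = 0.5 and 0.12 SD at ρ = 0.6. In 20,000 simulated trials, gaps between 0.15 and 0.25 SD carried over as 0.10 and 0.11 SD without adjustment, and as less than 0.004 SD in absolute value with it.

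**Step 5: no arm-by-time term.** Under exchangeable covariance the single arm effect weights the 10 visits equally.

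- Effect constant at 0.50 SD from month 2: 0.50 × 9/10 = 0.45 SD.
- Effect growing linearly from 0 to 0.50 SD at month 18: the mean visit is month 9, so 0.50 × 9/18 = 0.25 SD. Most of this shortfall comes from averaging the early follow-up visits, not from baseline alone.
- Under autoregressive covariance (correlation 0.90 or 0.93 between adjacent visits), the constant effect is estimated as 0.32 or 0.31 SD.

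This is dilution of the estimate, which is not the same as loss of power. At exchangeable ρ = 0.5 the pooled standard error is 0.143 SD. The constant effect then gives 0.45/0.143 = 3.15 standard errors, against 0.50/0.167 = 3.00 with a common baseline mean. The linearly growing effect gives 0.25/0.143 = 1.75.

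**The case against.** **Baseline as an outcome is not the error.** This is right. The common-baseline model also has baseline in the outcome vector, and keeping it there serves the within-arm effect sizes that the section promises. The free arm effect is inferred from two sections read together, and a condensed article might leave the parameterisation to the SAP. But the article does fix the outcome vector, the form of the arm term and the contrast, and taken together these imply no adjustment.

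**A reader might infer that baseline is ignored altogether.** That is too strong. It is exact only for a saturated arm-by-visit model with complete data and unstructured covariance. Under the attrition that Study limitations anticipates, a likelihood-based mixed model uses baseline to help recover missing month-18 scores. With linear time, baseline also enters the fit, although a free intercept still costs precision: standard error 0.158 against 0.122 SD at exchangeable ρ = 0.5.

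**The arm-by-time term may well be fitted.** A test at 18 months suggests it, and the plot inspection is described for employment data. Still, the secondary section adopts a similar method without fixing the term, so the dilution case remains open. The two cases are alternatives; only one applies to a given model.

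**A reader might take the early imbalance as proof.** Mean age is 44.4 against 54 years among the first 25 and 16 participants. The baseline tables report no psychological scores, so this shows only that chance imbalance can occur.

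**Conclusion.** The point holds as a loss of precision that can be avoided at no cost, with a possible dilution of the estimate. It is not a validity failure. With the arm-by-visit term, the unadjusted month-18 test is unbiased over randomization and keeps its type I error.

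The size depends on a correlation that the document does not give. At 0.3 the gain is small (9% of the variance); at 0.5 or above it is material (25% or more). These are upper figures, for complete data and a saturated model, and they rest on a sample size and detectable difference stated for the primary outcome. No stated power figure is contradicted. The dilution arises only if the arm-by-time term is omitted, and its size depends on the covariance structure and the time course of the effect.

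A reader might extend the point to the relapse and opioid-misuse models under MOUD analyses. The document does not support this: that section does not list the models' covariates, so no defect is stated there.

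**What to change.** Add a sentence to the Secondary outcomes analysis section that pre-specifies arm by categorical visit and one of two forms:

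- baseline stays in the outcome vector, the arm means are constrained to be equal at baseline, and arm effects are fitted at follow-up visits only; or
- only follow-up scores are outcomes, and the baseline score is a covariate.

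In either form, take the month-18 contrast as the test. The first form keeps within-arm effect sizes directly available, and it follows from the article's own expectation under Data analyses that randomization gives equivalent groups. The cost is a short text change and no new data. It is best made while follow-up is ongoing and no outcomes have been reported.

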
### Eligibility criteria

Eligible participants are (1) consenting US. military veterans who are ≥ 19 years of age; (2) currently unemployed or underemployed (i.e., working < 20 h/week in competitive employment, or currently employed in a job that is not meaningful or well-matched to the veteran); (3) desiring to work in a competitive job; and (4) have a history of current or lifetime OUD according to DSM-5. Veterans with a history of traumatic brain injury may be included as long as they do not have a severe cognitive disorder. The key to attaining and sustaining employment in the context of a recovery model is being recognized for the potential contributions one has made in the past and can once again address moving forward. Eligible veterans are either unemployed, marginally employed, or caught in the trap of working in entry level jobs unrelated to their past education, training and/or military experience. The absence of work or career choices with relevance or meaning to the veteran’s life can be a determinant of accepting and sustaining treatment adherence. Meaningful work is often described as employment in a valued environment or performing work tasks related to one’s personal preferences or life experiences, military or non-military.

Exclusion criteria include (1) a current diagnosis of schizophrenia, schizoaffective disorder or other psychotic disorders; (2) diagnosis of dementia or severe cognitive disorder; (3) presence of current severe and unstable medical condition or terminal illness, that would contraindicate study participation or expose them to an undue risk; (4) unlikely that participant can complete the study, e.g., expected deployment, incarceration, long-term hospitalization, or relocation from the vicinity; (5) active suicidal or homicidal ideation making it unsafe for the participant to be included; or (6) current participation in another vocational interventional trial.

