### Clinical assessments

At baseline, the Clinical Research Coordinator (CRC) collects baseline demographics and characteristics, including age, gender, race, ethnicity, marital status, education level, military history (i.e., branch, period of service, combat exposure), status of housing and transportation, status of VA and non-VA disability, psychiatric treatment history, past and current treatment for OUD, and work history, including length of unemployment, type of previous job(s), and longest duration of competitive work. The Mini-International Neuropsychiatric Interview for DSM-5 is conducted by an investigator or CRC to confirm OUD diagnosis and document comorbidities [23]. Repeated measures include: the Patient Health Questionnaire-9 (PHQ-9) [24]; the Generalized Anxiety Disorder Scale (GAD-7) [25]; Brief Resilience Scale (BRS) [26]; Perceived stress Scale-10 (PSS-10) [27]; Quality of Life Scale (QOLS) [28]; Community Assessment Inventory (CAI) [29]; Alcohol Abstinence Self-Efficacy (modified for OUD) [30]; the Tobacco, Alcohol, Prescription Medications, and Other Substance (TAPS) Part-2 Tool [31]; and the Columbia Suicide Severity Rating Scale (C-SSRS) [32].

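### The suicide-risk scale appears to fall under a month-18 mean-score test, a poor target for suicidal ideation or behaviour that comes and goes

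*Protocol article*

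**What the plan says.** Clinical assessments gives a single list of repeated measures. It opens with the PHQ-9 and GAD-7 and closes with "and the Columbia Suicide Severity Rating Scale (C-SSRS". Randomization and follow-up schedule sets visits at baseline, "every 2 months (months 2, 4, 6, 8, 10, 12, 14, 16) and then final assessment at month 18", so there are nine follow-up visits.

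Secondary outcomes analysis then states one rule for the group: "The effect of treatment on each of the psychological clinical measures will be analyzed using a longitudinal mixed-effects regression model". On the outcome it says "The dependent variable will be the outcome score at baseline and each follow-up time point", on time "Each follow-up visit will be categorized by the weeks since enrollment", and on the test "We will formally test for differences in outcomes at 18 months using predicted-marginal means". Secondary outcomes also go through a Benjamini–Hochberg procedure at 10%.

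The model is said to resemble the employment model. Under Primary outcome analysis, plots are to be examined to decide "whether it appears that a group*time interaction term is required to faithfully model the data".

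Eligibility criteria excludes "active suicidal or homicidal ideation making it unsafe for the participant to be included".

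**The concern.** For depression or quality of life, a mean score at the end of follow-up is a reasonable target. For suicide risk, the question of interest is whether ideation or behaviour emerged at any time after randomisation, and in how many people per arm. Such episodes can appear and resolve between visits.

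A contrast of mean scores at the last of nine visits answers a different question. If one arm had more participants with an episode at months 2 to 16 that had settled by month 18, the stated test could show little or nothing. A reader of the results could then take a null C-SSRS line as reassurance about harm.

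The article treats another episodic outcome differently. Under MOUD analyses, relapse measured by the TAPS tool (also in the repeated-measures list) is analysed as whether any relapse occurred, and as days of misuse. The C-SSRS has no counterpart to this.

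**Working it through.** The article gives no figure on suicidality, so there is nothing of its own to reproduce. Two checks apply.

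**1. How much weight does the month-18 contrast give to earlier visits?**

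Inputs: ten visits (months 0, 2, …, 18) from the follow-up schedule, with baseline included in the outcome as the secondary section states. Assumptions: complete data, and either exchangeable correlation of 0.5 or first-order autoregressive correlation of 0.7 between successive visits. The weights are those that generalised least squares places on the arm difference at each visit.

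| Mean model | Correlation | Month 18 | Each of months 2 to 16 |
|---|---|---|---|
| Categorical time × arm | either | 1.00 | 0 |
| Linear time × arm | exchangeable | 0.345 | −0.091 (month 2) rising to 0.291 (month 16) |
| Linear time × arm | autoregressive | 0.642 | 0.004 (month 2) rising to 0.132 (month 16) |
| No time × arm term | exchangeable | 0.10 | 0.10 |
| No time × arm term | autoregressive | 0.227 | 0.068 |

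Two rows can be checked by hand.
- Linear, exchangeable: the weight at month t is 1/10 + (18 − 9)(t − 9)/330, where 330 is the sum of (t − 9)² over the ten visits. Month 18 gives 0.1 + 81/330 = 0.345. Month 2 gives 0.1 − 63/330 = −0.091.
- No interaction, autoregressive: the two end visits each get 1/(10 − 8 × 0.7) = 1/4.4 = 0.227. The others get 0.3/4.4 = 0.068.

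So earlier visits receive exactly zero weight only in the first row. Categorised visits in the secondary section point towards that row, but the interaction is left to plots. Under the linear model with exchangeable correlation, an excess at month 2 or 4 would even count in the opposite direction. With no interaction, one episode is averaged over ten visits. If some participants leave early, their earlier scores gain some indirect influence through the model.

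**2. How many affected participants would not be positive at month 18?**

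The per-visit probability p is an assumption. If visits are independent, the proportion ever positive over nine visits is 1 − (1 − p)⁹, and the share of those not positive at month 18 is 1 − p/[1 − (1 − p)⁹].

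| p per visit | Ever positive | Positive at month 18 | Share of ever-positive not positive at month 18 |
|---|---|---|---|
| 2% | 16.6% | 2% | 88% |
| 5% | 37.0% | 5% | 86% |
| 10% | 61.3% | 10% | 84% |

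Independence is close to the extreme case. Ideation that persists or recurs in the same people narrows the gap.

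**The case against.** Several stronger readings are tempting, and the document does not support them.

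- *The C-SSRS is definitely in the score-model family.* The secondary section names no instrument, and the repeated-measures list is an assessment list. The TAPS tool shows that a listed instrument can have its own analysis. Inclusion is inferred, though nothing else is described for the C-SSRS.
- *Earlier suicidality drops out of the comparison.* Earlier scores are in the model, and they lose all weight under only one of the forms left open.
- *The trial would miss the events or reach a wrong safety conclusion.* Adverse and serious adverse events are assessed at every research visit, and an independent Data and Safety Monitoring Board oversees the study. The article describes no comparison of these events by arm, but a condensed article commonly leaves that to the full protocol or analysis plan.
- *False-discovery control suppresses a harm signal.* The procedure is offered as an aid to interpretation at a lenient 10%, and effect sizes with 95% intervals are reported as well.
- *Most scores sit at the floor.* Only ideation that makes inclusion unsafe is excluded, and no C-SSRS distribution is given. A floor is plausible but not shown.
- *A significant difference would be turned into a null one.* That depends on the split chosen. With 60 per arm, 12 versus 3 ever-affected participants gives a Fisher p of 0.025, but 12 versus 6 gives 0.20 even when every visit is counted.

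These points limit the strength of the claim. They leave the mismatch of target standing: under each model form, the only formal test is a mean-score contrast, and none counts the people in whom suicidality emerged.

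**Conclusion.** The concern holds in a limited form. Naturally read, the plan aims a month-18 mean-score test at a suicide-risk measure for which any occurrence during follow-up is the relevant outcome. Depending on the model finally chosen, a resolved episode gets no weight, reduced weight or diluted weight. The practical harm is a misleading line in the results; loss of safety oversight is not shown.

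The conclusion rests on the C-SSRS being one of the psychological measures meant by the rule, and on it being administered at all follow-up visits. The 84% to 88% range is an illustration under assumed rates and independence, and should not be quoted as an estimate for this trial. The point deserves correction but does not touch the primary analysis.

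**What to change.** State whether the secondary rule covers the C-SSRS. If it does, remove the scale from the month-18 mean-score test and from the Benjamini–Hochberg family. Report instead, by arm, the number of randomised participants with any post-baseline suicidal ideation and, separately, with any suicidal behaviour, at any visit through month 18. Give the risk difference with an exact 95% confidence interval, and show participants positive at baseline separately.

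The cost is analysis wording only. The scale is already a repeated measure, and the article reports enrolment and follow-up as still under way with no outcomes presented. The secondary table loses one line, and intervals will be wide for rare events. For example, 12/60 versus 6/60 is a difference of 0.10 with standard error √(0.2 × 0.8/60 + 0.1 × 0.9/60) = 0.065. The approximate 95% interval is −0.03 to 0.23, and an exact interval would differ somewhat. The summary should therefore be presented as descriptive safety information, with no claim that it is a powered test.
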